**Experimental design and methods to be used in investigating these scientific questions**

###### i) Overall study design

# We propose to conduct an open, randomised controlled trial (RCT) of reactogenicity and immunogenicity of a 7-valent Pnc-CRM197 conjugate vaccine (Prevenar) in 312 infants in the Asaro Valley, PNG, where extensive population- and hospital-based research has been conducted into the epidemiology and prevention of ALRI (6). Following ethical approval, principally by the PNG Medical Research Advisory Committee (MRAC) and also by the respective institutional review boards in Australia, demographic surveillance will be established in villages of Lowa Census Division (CD). Pregnant women will be enrolled in these villages and also at the Goroka Hospital antenatal clinic. Following delivery, infants will be randomised to one of three equal-sized groups to receive: 1) PCV at ages 0-1-2 months, 2) PCV at ages 1-2-3 months and 3) no PCV in addition to routine infant immunizations and PPV at age 9 months. Table 1 shows the vaccines given, samples collected and surveillance maintained. Nasopharyngeal Pnc colonisation will be assessed frequently for the first 4 weeks of life and at regular intervals thereafter to look for effects of early colonisation on subsequent immune responses to PCV and vice-versa. Infants will undergo comprehensive immunological evaluation for systemic and mucosal antibody responses, T-cell-specific cytokine responses, induction of immunologic memory for PCV CPS and antibody avidity maturation. We will also examine kinetics of postnatal maturation of humoral and T-cell immunity over time.

### Table 1. Neonatal Immunization with Pnc Conjugate Vaccine Study Outline

|  | Birth | 1 -3wk | 1mth | 2mths | 3mths | 4mths | 6 mths | 9mths | 10mths | 18mths |
| --- | --- | --- | --- | --- | --- | --- | --- | --- | --- | --- |
| Group 1 Neonatal PCV | HepB, BCG, OPV, PCV |  | DTP/Hib, HepB, OPV, PCV | DTP/ Hib, OPV, PCV | DTP/ Hib, OPV, HepB |  | Measles | PPV Measles |  |  |
| Group 2 Infant PCV | HepB, BCG  OPV |  | DTP/Hib, HepB, OPV, PCV | DTP/Hib, OPV, PCV | DTP/Hib, OPV, HepB, PCV, |  | Measles | PPV Measles |  |  |
| Group 3 Control | HepB, BCG  OPV |  | DTP/Hib, OPV, HepB | DTP/Hib, OPV | DTP/Hib, OPV, HepB |  | Measles | PPV Measles |  |  |
| Nose Swab |  | weekly | X |  | X |  |  | X |  | X |
| Saliva 1-2 ml |  |  | X | X | X | X |  | X | X | X |
| Serum 2-4 ml | **X*** |  |  | X | **X** | **X** |  | **X** | **X** | **X** |
| PBMC 3-5ml | **X*** |  |  |  | **X** |  |  | **X** | **X** | **X** |
| Morbidity surveillance |  |  |  |  |  |  |  |  |  |  |

HepB: hepatitis B vaccine; PCV: 7-valent Pnc-CRM197 conjugate vaccine; OPV: oral polio vaccine; DTP: diphtheria-tetanus-whole-cell pertussis; Hib: *Haemophilus influenzae* type b tetanus toxoid conjugate vaccine (PRP-T); PPV: 23-valent Pnc polysaccharide vaccine

***** Cord blood sample: total 10ml taken for PBMC (peripheral blood mononuclear cells)

# Demographic surveillance and recruitment of study participants

After informing communities about the study, a house-to-house census will be undertaken in those villages previously under surveillance in Lowa CD. Surveillance by local reporters will identify pregnant women, ensure close monitoring for safety of neonatal immunization for 18 months post-vaccination and re-establish a population base for future studies including an efficacy trial of neonatal PCV if appropriate. If necessary, surveillance will be extended to neighbouring villages to include a total population of more than 3000 in order to identify 100 pregnant women annually. A nurse will also recruit women through antenatal clinics at Goroka Hospital to enrol an equal number of urban children. In view of the intensive monitoring schedule, no more than 2 urban and 2 rural mothers will be recruited weekly. Data on URT carriage rates in the urban population are not available; however, we might expect later onset of URT Pnc carriage in babies living in the less crowded, more hygienic urban living conditions. By enrolling equal numbers of participants from urban and rural areas we can investigate the effect of early onset of carriage on subsequent immune responses. Following enrolment at antenatal clinic, a home visit will be done to collect social and demographic data on the entire household (for comparison between urban and rural areas). This will help re-establish an urban population base for future trials. Weekly surveillance of all households in enlisted villages and of enlisted families in Goroka will continue for the entire study period for safety monitoring, identification of potential new participants, registration of deaths and migrations in and out of the area. Each person under demographic surveillance is assigned a unique identifying number used to link all data.

# Enrolment of study participants and consent

Once staff have been trained and a village is under weekly surveillance, pregnant women can be enrolled, while continuing to expand the demographic base. Informed consent will be sought antenatally. The standard process for obtaining informed consent for studies in PNG, as used and documented by the PNGIMR and approved by the Medical Research Advisory Committee of PNG (MRAC), will be followed. Information will be collected on parity, number of antenatal attendances, illness and treatment given during pregnancy and timing of routine maternal immunization with tetanus toxoid. PNGIMR will assist with transport to encourage women to attend antenatal clinics and deliver at Goroka Hospital.

# Inclusion criteria and recruitment

Infants of women intending to remain in the area for at least 2 years with a birthweight >2000 g, no acute neonatal infection and no severe congenital abnormality will be recruited. The majority of babies selected for the study will be born in hospital, but children born at home may also be included if appropriate. Note that not all mothers enrolled will have babies recruited to the study, depending on the number born in any particular week, collection of a cord blood sample and condition of the baby. Formal recruitment will begin with the routine vaccinations (BCG, OPV, HepB), which should be given within 72 hours of birth. While there will be no routine HIV testing, children of mothers known to be HIV positive will be excluded. Computer-generated lists of random numbers will be used for block randomization (see vii below).

# Immunization schedule and follow-up

Village reporters will inform study staff if a woman has delivered outside hospital. A study nurse will visit the delivery ward at Goroka Hospital at least once daily to identify newborns to enrolled women. Following recruitment, infants will be randomized to one of three equal-sized groups to receive: 1) PCV at ages 0-1-2 months, 2) PCV at ages 1-2-3 months and 3) no PCV. Birthweight and weight at each follow-up visit will be recorded. Routine infant immunizations will be given in accordance with the PNG schedule (Table 1). As PCV has not been evaluated in this population previously, the first 52 infants will be randomized to groups 2 or 3 only, and the safety data will be reviewed by an independent safety monitoring committee. Conjugate Hib vaccine (ActHib), which is mixed with DPT, has recently been introduced into the immunization schedule in PNG, after being shown to be safe and immunogenic in this population when given at ages 1, 2 and 3 months (76). Since it is in short supply, we may have to purchase it. BCG and DPT/Hib are routinely administered in the deltoid muscle. Hepatitis B and measles will be given in the right thigh. PPV (at 9 months) and PCV will be given in the left thigh.

All immunizations will be given either in Goroka Hospital or at the PNGIMR clinic. Following immunization, children will be monitored at the clinic for 2 hours. Children will then be seen 1 and 2 days after each dose during primary immunization and on day 7 following PPV to check for local or systemic reactions. Children will be seen weekly by nursing staff to age 4 weeks. Guardians will be informed of time of appointments and transport to Goroka clinic will be arranged. If they fail to attend their appointment, we will make 3 further attempts to bring the children for routine follow-up. Guardians may choose to remove their child from the study at any time. Participants will cease to be in the study if they suffer an allergic reaction to vaccination or have inadvertently been given routine immunizations by someone other than the study nurses. All such children will continue to receive medical attention from clinic and field staff as required.

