# Morbidity surveillance

Throughout the first year of life reporters will complete morbidity reports, which will be reviewed weekly by medical staff and then fortnightly to age 18 months. Parents will be encouraged and assisted to bring children in to the PNGIMR for examination and treatment if sick. Blood culture and nasal swab will be done on children with cough and raised respiratory rate (77). Children with moderate pneumonia (lower chest wall indrawing) or severe pneumonia (chest indrawing and enlarged liver or cyanosis) will be hospitalised; blood culture, nasal swab and a chest x-ray will be taken. CXRs will be read by the senior physician ([name]) and a sample then reviewed by a radiologist recommended by the WHO radiology group.

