PNG infants remain at ongoing risk of IPD in the first 5 years of life. Long-term protection induced by PCV depends on the successful priming for immunologic memory so infants can mount brisk anamnestic antibody responses on subsequent challenge. All infants will receive 23-valent PPV at 9 months of age (6 months after their primary course) to evaluate the induction of memory to PCV serotypes. These serotypes in PPV are not immunogenic in PNG infants at age 9 months (except for 23F) (24) so that significant IgG responses to PCV serotypes compared to PCV-naive controls will indicate the induction of memory. This vaccine is efficacious from age 6 months and provides some cover against serotypes which are important causes of IPD in this population. Antibody avidity maturation (post-primary to post-booster immunization) will also be assessed as it is a surrogate marker for the induction of memory after conjugate vaccines (39, 80, 81) and influences the functional capacity of antibodies produced (35). Avidity maturation will be assessed by comparing changes in avidity index between 4-, 9- and 10-month samples in comparison to controls. Antibody persistence will be evaluated with blood samples at 18 months of age.

*4. The impact of neonatal versus early infant vaccination upon nasal carriage of pneumococci*

Reduction in the burden of early Pnc carriage in the critical neonatal period may have an important impact on early disease as well as the development of long-term immunity to Pnc infections. Regular carriage sampling in the first month of life will assess the impact of neonatal PCV immunization, and carriage will be assessed at regular intervals thereafter to determine persisting effects of PCV on carriage compared to controls.

*5. The impact of early colonisation with vaccine serotypes on antibody responses (systemic and mucosal) to neonatal and early infant immunization with PCV*

In the Asaro Valley 60% of infants acquired Pnc in the URT by 15 days of age. PCV serotypes are responsible for 59% of carriage isolates in the first 3 months of life in PNG (16). Swabs will be collected at weekly intervals during the first month to identify children with early ( 2 weeks) colonisation. This will allow evaluation of the effects of early colonisation on systemic antibody responses to subsequent PCV immunization. Effects of time of colonisation and PCV on mucosal immunity (salivary IgA responses to Pnc CPS and OMPs) will also be assessed .

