Invasive and mucosal Pnc infections in early infancy are a major global health burden. The potential advantages of neonatal immunization include high vaccination coverage, protection against very early Pnc carriage, reduction in mortality and morbidity due to pneumonia and IPD in early infancy, and enhancement of subsequent protection by PPV. Benefits are also likely to occur for the prevention of OM and its complications in high-risk populations. Detailed studies are essential to ensure “immunological safety” of this approach and to further our understanding of mechanisms of actions of bacterial conjugate vaccines. Public concerns over increasing numbers of vaccines overloading children’s immune system mean that in-depth immunological studies are needed globally to provide a solid basis for ensuring the safety of immunization in infants and to address these safety concerns explicitly. This study will provide basic immunological understanding to inform the epidemiological investigation of the immune responses achieved and the safety and possible non-specific benefits of immunization in a tropical setting. Furthermore, the results of this study will be particularly relevant for the prevention of Pnc disease in the ‘fourth world’ – in young indigenous children of first world countries who suffer similarly high rates of Pnc disease and early URT carriage.

Australian investigators will gain expertise in field research in non-industrialised countries, which will help enhance collaboration with groups in other countries in the region. Through detailed investigation of immune responses in infants exposed to numerous pathogens from a very young age, this collaboration will complement studies conducted in Australia towards understanding the development of the immune system in infancy.

This proposed study will have important implications for the development of pneumococcal immunization policy in PNG and other non-industrialised countries. If neonatal immunization with PCV is found to be safe, the collaborators will be in a strong position to proceed to an efficacy study and work towards establishing the most effective and cost-efficient schedules for PCV and the associated use of PPV.

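### After PPV the only scheduled reaction check beyond the clinic stay is on day 7, against days 1 and 2 for primary doses, so short-lived PPV reactions may be under-recorded

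*Protocol*

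**What the plan says.** Under Immunization schedule and follow-up, the protocol has children "seen 1 and 2 days after each dose during primary immunization and on day 7 following PPV to check for local or systemic reactions". The same section provides a short observation for every vaccine: "Following immunization, children will be monitored at the clinic for 2 hours". It places PPV and PCV in the left thigh and measles vaccine in the right.

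Table 1 and question 3 of section vi show PPV given at 9 months in all three groups. Table 1 also shows measles vaccine at that visit in all three groups. Question 3 explains that PPV tests whether "infants can mount brisk anamnestic antibody responses on subsequent challenge".

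Other safety nets run alongside. Morbidity surveillance: "Throughout the first year of life reporters will complete morbidity reports, which will be reviewed weekly by medical staff", and parents are helped to bring in sick children. Demographic surveillance: "Weekly surveillance of all households in enlisted villages and of enlisted families in Goroka will continue for the entire study period", with safety monitoring among its stated purposes. The safety monitoring board section asks that all adverse events be reported. None of these describes a scheduled look at the injection site on days 1 or 2 after PPV.

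**The concern.** By examining infants on days 1 and 2 after each primary dose, the protocol itself treats those days as the time to see reactions. A single look on day 7 does not serve that purpose equally well, and no argument is offered that PPV reactions come later or last longer.

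PPV is also the dose at which the randomised groups differ in priming. Whether infants given PCV at 0-1-2 or 1-2-3 months react more to a later polysaccharide dose is a natural tolerability question about those schedules, and the trial already contains the comparison. The section on expected outcomes looks ahead to "establishing the most effective and cost-efficient schedules for PCV and the associated use of PPV". Early reaction data that were never collected cannot be recovered at analysis.

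**Working it through.** There is no figure in the plan to reproduce, because no stated sample size, power or error rate depends on this visit. The check is a comparison of text, followed by an illustration.

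**Text.**
- Primary doses: 2 hours in clinic, then days 1 and 2.
- PPV: 2 hours in clinic, then day 7.
- Days 1 to 6 after PPV: weekly reporter contact, care-seeking if the child is sick, and reporting of adverse events that come to notice. No scheduled reaction check.

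**Inputs.** From section vii: 100 per group, at least 90 evaluable, 5% significance (taken as two-sided). Assumed, with no source in the protocol: true reaction proportions of 10% (PCV-naive) and 30% (primed), and a share f of reactions still visible or recalled on day 7, equal in all groups.

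**Formula.** The observed proportions become 0.10f and 0.30f. The difference is 0.20f; their ratio is unchanged. With pooled proportion 0.20f,

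power = Φ[(0.20f − 1.96·SE0)/SE1], where SE0 = √(2·0.20f·(1 − 0.20f)/n) and SE1 = √([0.10f(1 − 0.10f) + 0.30f(1 − 0.30f)]/n).

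Example, n = 90 and f = 1: SE0 = 0.0596, SE1 = 0.0577, so (0.20 − 0.1169)/0.0577 = 1.44 and power is 92.5%.

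**Illustration A: f set directly, n = 90.**

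| f | Observed | Power |
|---|---|---|
| 1 | 10% v 30% | 92.5% |
| 0.75 | 7.5% v 22.5% | 81% |
| 0.5 | 5% v 15% | 61% |
| 0.25 | 2.5% v 7.5% | 34% |
| 0.1 | 1% v 3% | 16% |

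**Illustration B: f from an assumed duration, n = 100.** If reactions present on day 2 resolve exponentially with mean d days, and only those still visible on day 7 are recorded, then f = exp(−5/d). Power with everything captured is 95%.

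| d (days) | f | Observed | Power |
|---|---|---|---|
| 1.5 | 0.036 | 0.4% v 1.1% | 9% |
| 2 | 0.082 | 0.8% v 2.5% | 15% |
| 3 | 0.189 | 1.9% v 5.7% | 29% |
| 5 | 0.368 | 3.7% v 11.0% | 51% |

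Using 90 instead of 100 in B lowers these by at most about 4 percentage points. The normal approximation is rough where about one event or fewer is expected per group. The direction is the same throughout; the size depends on f.

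**The case against.** The best defence is that the intensive visits belong where they are. The overall study design section states reactogenicity as an objective for the 7-valent PCV, not for PPV. For PPV the aims promise a closer immunologic evaluation, and no PPV reaction endpoint or comparison is named. PCV is the vaccine new to this population; the background reports PPV trials in PNG children from 6 months of age and PPV boosting in Australian indigenous children. This stands, and it is why the point is minor. It does not explain why the same stated purpose is served by two windows. Since PCV has not been evaluated in this population before, the PNG experience with PPV does not cover PCV-primed infants.

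A reader might infer that any PPV reaction will be over before anyone looks. The protocol does not support that. There is the 2-hour observation, the weekly surveillance and assisted attendance, and no duration of PPV reactions is given. Severe or prolonged reactions could well be noted. The day-7 check is also not limited to signs present that day: the form is not shown, so it cannot be said that guardians are not asked about the preceding days.

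A reader might also infer that measles vaccine at the same visit spoils the comparison. It does not. All three groups receive it, so its fevers are balanced by randomisation, and local reactions are separable by thigh. Only the cause of an individual child's fever stays uncertain.

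Finally, higher reaction rates in primed infants are a hypothesis. The brisk response that the protocol expects is of antibody, and it nowhere links this to reactions.

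**Conclusion.** The difference in timing is plain from the text and unexplained. Followed as written, the schedule is likely to record short-lived PPV reactions less completely than reactions to primary doses, and the absolute difference between groups 1 and 2 and group 3 is then biased toward zero. This assumes that the captured share is below one and similar across groups; reactions that last longer in primed infants would alter the dilution.

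The size cannot be fixed from the protocol. Under the assumed 10% v 30%, power falls from about 92.5–95% to somewhere between about 9% and 81%. It would be tempting to conclude that the trial would report no excess of PPV reactions almost whatever the truth. That goes too far, since it rests on assumed rates, assumed durations and a day-7 check that ignores recent history. Nor does the passage on future schedules say that PPV reaction data from this trial will decide them; it describes later work. Severity is minor.

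**What to change.** Reconcile the two assessment windows, or state why they differ. Two ways need no extra visit:

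1. Keep day 7, and record the onset date and duration of any left-thigh reaction or fever since the injection. Cost: a dated question on the form if it is not already there, and reliance on 7-day recall. Because the trial is open, that recall could differ by group, so the question should be worded identically for all.
2. Place the single nurse check in the window used for primary doses. Cost: later reactions are left to the weekly surveillance, which is not an injection-site examination.

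Under either option, compare groups 1 and 2 with group 3 on early reactions, and describe this as a secondary safety comparison. Only data collection changes.

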**iii) Safety monitoring board**

A safety monitoring board (SMB) will be established, including independent clinicians from PNG and Australia. If the board finds nothing untoward following the first block of 52 immunizations of groups 2 and 3, the trial will then be authorized to proceed including neonatal immunization (group 1). Clinical and immunogenicity data will be sent regularly to the clinical monitors. Throughout the study, all adverse events will be reported and any serious adverse events will be immediately reported to the SMB. In particular, they will examine the data for any evidence of tolerance/immune suppression in addition to serious adverse events.

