**vii) Sample size requirements**

**Urban Rural n**

Group #2 #3 #1 #2 #3 #1 312

Block 1 13 13 13 13 52

Block 2 13 13 26 13 13 26 104

Blocks 3-4 26 26 26 26 26 26 156

The block randomisation schema is set out above. The sample size requirements were based on the primary questions and assumed 80% power and a 5% significance level. Distributions of published Pnc vaccine responses (21, 43, 44) indicate a standard deviation of serotype-specific IgG concentration of around 1 on the natural logarithmic scale, at all ages. For serious adverse reactions in Block 1, 26 subjects will be allocated to the post-neonatal PCV group 2 and 26 to the control group 3. This comparison will allow proportions of adverse events of e.g. 10% in the control group versus 48% in the treated group, or 5% vs 40%. If no serious adverse events occur in the first 26 treated children, it is likely that the true adverse event rate is 10% or less (and similarly in Block 2 for neonatal PCV group 1). Given 70% seroprotection (>0.5g/ml) after 1 dose of PCV at age 6 weeks (43), the sample size of 100 per group (min. 90 evaluable) allows this proportion to be estimated with 95% CI of 60-79% and will have 80% power at the 5% significance level to detect a 20% difference from group 1 (i.e. 90%) or group 3 (i.e. 50%).

For ALRI hospital admissions, assuming a rate of 0.0425 per child month under 1 year, a 50% decrease in either vaccinated group compared with controls is detectable. We can detect differences in carriage rates between the groups from 1 month onwards of say 40% down to 22% or lower.

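### An allergic reaction or an outside routine vaccine ends study participation rather than study vaccination alone, so later outcomes of randomised infants are not provided for

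*Protocol*

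**What the plan says.** Section ii) Field methods, Immunization schedule and follow-up, sets the order of events. Allocation comes first: "Following recruitment, infants will be randomized to one of three equal-sized groups". The exit rule acts later: "Participants will cease to be in the study if they suffer an allergic reaction to vaccination or have inadvertently been given routine immunizations" from anyone other than the study nurses. What follows an exit is one sentence: "All such children will continue to receive medical attention from clinic and field staff as required". No study visit, swab, blood sample or outcome record is mentioned for these infants.

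Three other places bear on the point:

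- Section iii) Safety monitoring board: "Throughout the study, all adverse events will be reported and any serious adverse events will be immediately reported to the SMB". The board is also asked to look for signs of tolerance or immune suppression.
- Demographic surveillance and recruitment: surveillance by local reporters is meant, among other purposes, to "ensure close monitoring for safety of neonatal immunization for 18 months post-vaccination". It also says: "Weekly surveillance of all households in enlisted villages and of enlisted families in Goroka will continue for the entire study period for safety monitoring", and it lists registration of deaths.
- Section vii) Sample size requirements: the calculations "assumed 80% power and a 5% significance level" and give "the sample size of 100 per group (min. 90 evaluable").

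Safety and first-year respiratory morbidity both appear in the Aims of the Study. Table 1 gives three PCV doses to groups 1 and 2 and none to group 3. Section i) describes the trial as open.

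**The concern.** The rule joins two decisions that should be separate: whether an infant gets further study vaccine, and whether the infant's outcomes are still collected. It ends both because of events that happen after randomisation.

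The first trigger is a safety outcome, and exposure to it differs by design between the PCV groups and the controls. The second depends on care-seeking and mobility, and families know their allocation, so it too may differ between groups. If exits differ by group, the infants who remain are no longer the groups that were randomised. Later comparisons of adverse events, admissions, carriage and antibody are then open to selection bias.

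A statistical analysis plan can define analysis sets, but it cannot recover follow-up that was never collected. That makes this a matter for the protocol.

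**Working it through.** **Inputs.** From section vii): 100 per group with at least 90 evaluable; 312 in total over three groups, so 312/3 = 104; 26 treated infants in the Block 1 safety look; 80% power at the 5% level (two-sided assumed); seroprotection of 70% against 50% or 90%; 0.0425 ALRI admissions per child-month, with a halving to be detected. No exit rate is given anywhere.

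**Step 1: the plan's own figures.**

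Power for two proportions is Φ{[|p1−p2|√n − 1.96√(2p̄(1−p̄))] / √(p1(1−p1)+p2(1−p2))}. For 70% v 50% at n = 90 this is Φ[(1.897 − 1.358)/0.678] = 78.7%. At n = 100 it is 82.8%. For 70% v 90% at n = 90 it is 92.5%.

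For ALRI admissions over 12 months, the expected counts at n = 100 are 0.0425 × 12 × 100 = 51.0 and 25.5. Power is Φ[ln 2/√(1/51.0 + 1/25.5) − 1.96] = 81.5%. At n = 90 it is 77.4%.

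For zero events in 26, the one-sided 95% upper limit is 1 − 0.05^(1/26) = 10.9%.

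These agree with the protocol to within rounding or a few points. The point does not rest on an error in the sample size.

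**Step 2: what one exit costs.**

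- Of a 26-infant safety group: 1/26 = 3.8%.
- Of the stated allowance: 100 − 90 = 10 infants, so one exit uses a tenth. As an assumed range, 1 to 10 exits per group would use between 10% and all of it, before any other loss.
- Of follow-up: an infant who exits at 1 month (assumed) loses 18 − 1 = 17 months. That includes 11 first-year child-months, or 11 × 0.0425 = 0.47 expected admissions at the planning rate.

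**Step 3: how far a small safety group could be misread.** This is a worst case by assumption: each of k exited infants later has a serious event that is not counted.

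| k | Seen | Upper 95% limit | True | Upper 95% limit |
|---|---|---|---|---|
| 1 | 0/25 | 11.3% | 1/26 | 17.0% |
| 2 | 0/24 | 11.7% | 2/26 | 22.3% |
| 3 | 0/23 | 12.2% | 3/26 | 27.2% |

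The limits are one-sided. The table shows sensitivity, not expectation.

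**Step 4: direction.** Suppose a fraction e of a group exits, and these infants have r times the event rate of those who stay. The rate among those who stay, divided by the rate in the whole group, is 1/(1 − e + er). This is below 1 if r > 1 and above 1 if r < 1. The documents give neither e nor r for any group, so the sign cannot be derived.

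**Step 5: retaining everyone.** With all 104 followed, power is 84.3% for 70% v 50% and 83.0% for the halved admission rate. At 90 evaluable the figures are 78.7% and 77.4%. The change needs no larger sample.

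**The case against.** Four points can be made for the protocol.

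*The reaction is not lost.* Infants are observed for two hours and seen one and two days after each primary dose, and all adverse events are reported. The allergic reaction is therefore on record before the exit rule acts. This stands. A reader might infer that the safety data omit the reactions themselves; the protocol does not support that. Only what follows the exit is at risk.

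*Surveillance continues.* Weekly visits cover every household in enlisted villages, register deaths and use a linking identifier, so a rural infant who exits remains visible. This stands in part. In Goroka only enlisted families are covered, and nothing says whether an exited infant's family stays enlisted. Nor does the protocol say that data on exited infants will be used as study outcomes. For the same reason it is too strong to call the 18-month safety commitment and the exit rule a contradiction. The protocol is silent on exited infants, and that gap is what needs closing.

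*Bias towards the vaccine is not shown.* A reader might infer that adverse-event rates in the PCV groups will be understated. All groups receive the routine vaccines and PPV, the rule covers a reaction to any of them, and no exit rates are given. Neither direction nor size can be claimed.

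*Excluding off-schedule infants has a rationale.* The primary outcome is serotype-specific IgG at 2 months, and interference with concomitant vaccines is an aim, so uncontrolled routine doses can blur both. This supports a secondary immunogenicity analysis without the affected samples. It does not support ending safety, morbidity or carriage follow-up. Which infants enter which analysis could be left to the analysis plan; whether they are followed could not.

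**Conclusion.** The concern holds as a design weakness in a stated rule. Randomised infants leave the study because of post-randomisation events, one of which is a safety outcome that can depend on allocation, and no study follow-up is provided for them afterwards.

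The firm part of the size is per exit: 3.8% of a 26-infant safety group, and one tenth of the stated allowance of 10. A reader might take the allowance to be 14, from 104 down to 90, but the protocol's own statement starts from 100. Everything beyond that rests on assumption. The number of exits, their split between groups and their later event rates are not in the document, and the worst-case table requires every exited infant to have a later uncounted event. The sample size itself is not at fault.

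**What to change.** Amend the exit sentence in Immunization schedule and follow-up so that meeting either criterion does not end study follow-up. Unless the guardian withdraws consent, these infants should:

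- stay in adverse-event, morbidity, admission, death and carriage follow-up to 18 months, with blood sampling if the guardian agrees;
- be analysed in the group to which they were randomised.

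Add a secondary immunogenicity analysis that excludes samples taken after the deviation. Record the date and reason for each deviation by group, so that the extent of the problem can be reported. Whether vaccination continues after a reaction is a clinical decision and should be stated separately.

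The cost is small: a short amendment, a check that the consent wording covers continued follow-up, and some extra visits for children whom clinic and field staff already see. The downside is slight dilution of the immunogenicity comparison by off-schedule infants, which the secondary analysis addresses.
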